**Table 5. Post-therapy evaluations.**

| Test/Assessment/Sample | Post-Study Visit 1 | Post-Study Visit 2 |
| --- | --- | --- |
|  |  |  |
| Physical examination |  | X |
| Vital signs/Karnofsky Performance Status |  | X |
| CBC, with differential and platelet count | X | X (1) |
| Serum chemistries | X | X (1) |
| Flow cytometry | X | X (1) |
| Plasma virology sample | X | X (1) |
| Whole Blood for PBMC’s | X | X (1) |

(1) These procedures are to be completed within 2-14 days after commencement of post-therapy visit 1.

### E. Statistical considerations

### 1. Endpoints

The primary endpoint will be the time-weighted mean change in CD4+ cell count from baseline and time-weighted mean change in plasma HIV-RNA from baseline.

Secondary endpoints will include safety data.

### 2. Sample size

Based on an estimate of within patient variability corresponding to a standard deviation of 150 cells/mm3 (data on file), and using a two-sided significance level of 5%, a total of 36 patients randomized in the ratio of 2 SC IL-2:1 control participant will give 80% power of detecting an increase in the SC IL-2 group of 150 cells/mm3 (175 cells/mm3 with 20% dropout).

Based upon an estimate of within patient variability corresponding to a standard deviation of 0.7 log copies/ml (Eron J et al, NEJM 1995; 333:1662-9), and using a two sided significance level of 5%, a total of 36 patients randomised in the ratio of 2 SC IL-2: 1 control participant will give 80% power to detect a 0.7 log copies/ml difference between treatment groups (0.8 log copies/ml with 20% dropout).

### 3. Analysis of data

The final analysis will be conducted once all randomized patients have completed completed the study as described OR one year following initiation of the study. There will be no interim analyses of efficacy data for the purposes of early study termination.

a) Patient characteristics

Patient characteristics at baseline will be summarized by randomized treatment using appropriate summary measures. Patient characteristics to be summarized will include age, sex, baseline CD4+ cell count and virus load. There will be no formal comparisons of baseline characteristics performed.

b) Efficacy parameters

All efficacy data will be analyzed by the intent-to-treat principle. In particular, all doses of SC IL-2 used in the escalation phase will be included in the data from treated patients.

The change from baseline in CD4+ cell count and virus load will be summarized at each sampling time point. Formal analysis will compare the randomized treatments in terms of time-weighted changes from baseline using ANOVA methods, or equivalent non-parametric methods as appropriate.

c) Safety

Safety data will be summarized by treatment received for each time point.

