# V. STUDY DESIGN

### A. OVERVIEW

This is a phase II open label study of escalating doses of subcutaneous (SC) IL-2 alone versus no therapy in patients with HIV infection and a CD4+ lymphocyte count of at least 350 cells/mm3. This protocol is intended to define the safety and tolerability, immunological superiority and virological neutrality of IL-2 immunotherapy over no therapy.

There will be 3 treatment arms (1 control; 2 IL-2). Eligible patients will be randomized to receive no therapy or IL-2 therapy with two discreet doses of SC IL-2 (delivered for five days every eight weeks).

A total of 36 patients will be required to complete a minimum of three cycles of treatment. Of these patients, 12 will be allocated to receive no therapy and 24 patients will receive SC IL-2. A cycle is defined as 8 calendar weeks to include as necessary one five day period of SC IL-2 therapy.

Dosing with SC IL-2 will commence at doses of 4.5 MIU or 7.5 MIU twice daily (q12h) for 5 days every eight weeks. No patient will be treated with more than 7.5 MIU q12h x 5 days every eight weeks and no patient will commence a treatment cycle at a dose of less than 1.5 MIU q12h x 5 days every eight weeks.

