### D. Post-therapy evaluations

Post-therapy evaluations will be conducted on all patients. These evaluations must be completed in the time frame indicated by the following instructions:

- IL-2 treated patients who complete 3 cycles of therapy as described by this protocol should commence post-therapy evaluations no earlier than 8 calendar weeks after commencing the final cycle of IL-2.
- patients who have permanently discontinued IL-2 prematurely as a consequence of toxicity or any other reason, should commence post-therapy evaluations no sooner than 8 weeks after commencement of their most recent treatment cycle.
- control patients should commence post study evaluations no earlier than 24 weeks after entering study.

Post therapy evaluations consist of tests, procedures and samples as shown inTable 5:

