**II. REAGENTS**

A. Monoclonal Antibody Panel

ANTIBODY MANUFACT. CAT.# VOL/TEST

| **Limited Flow Panel (1-3)** | | | |  |
| --- | --- | --- | --- | --- |
| 1. IgG1 FITC x IgG2 PE | B-D1 | 335041 | 20 µL | |
| 2. CD3 FITC x CD4 PE | B-D | 335043 | 20 µL | |
| 3. CD3 FITC x CD8 PE | B-D | 349519 | 20 µL | |
|  |  |  |  | |

In addition, the following may be performed:

C.Neg.IgG1 FITC

C.Neg.IgG1 PE

CD45/CD14 (Leucogate)

CD3 PE

CD4 FITC

CD8 FITC

CD38 PE

CD45 RO Pe

CD45 RA FITC

For a total of 840 tests during a period of two years, 5 vials of each of the monoclonal antibodies are needed.

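### The final analysis may run one year after study start without saying whether that date or patient completion governs; taken as the earlier date, it can cut the primary comparison short

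*Protocol*

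**What the plan says.** Section VIII.E.3 of the protocol (Analysis of data) schedules the final analysis for when all randomized patients "have completed completed the study as described OR one year following initiation of the study". It does not say whether the earlier or the later condition applies, what counts as initiation, or what happens to patients still on study at one year.

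The rest of the protocol is built on completed follow-up:

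- Section V.A (Overview): "A total of 36 patients will be required to complete a minimum of three cycles of treatment", and "A cycle is defined as 8 calendar weeks".
- Section VIII.D (Post-therapy evaluations): IL-2 patients who finish three cycles "should commence post-therapy evaluations no earlier than 8 calendar weeks after commencing the final cycle of IL-2", and "control patients should commence post study evaluations no earlier than 24 weeks after entering study". Table 5 then places the second closing visit 2 to 14 days after the first.
- Section VIII.E.1 (Endpoints): "The primary endpoint will be the time-weighted mean change in CD4+ cell count from baseline and time-weighted mean change in plasma HIV-RNA from baseline". No period is given over which the mean is taken.
- Section VIII.E.2 (Sample size): the stated 80% power rests on 36 patients randomized 2:1.

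No accrual period or rate is stated. Section IV lists the rate of recruitment among the things the study is to assess.

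**The concern.** A calendar trigger that can fire first conflicts with the requirement that 36 patients complete three cycles. It is fixed in the protocol, so it is not simply a detail left to the analysis plan.

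If it fired early, late entrants would contribute means over shorter periods with fewer IL-2 cycles. Two features make this more than a loss of precision. First, a time-weighted mean without a horizon can be computed over any length of follow-up, so the quantity being estimated changes with entry date. Second, the arms are not sampled alike early on. Table 3 gives IL-2 patients a virology sample at day 8 of cycle 1, and flow cytometry and virology at day 29. Table 4 gives controls nothing between week 0 and week 8. A short record therefore holds different information in each arm.

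**Working it through.** **1. The plan's own figure.** With 12 controls, 24 IL-2 patients, difference 150 and SD 150 (Sample size section):

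power = Φ(150 / (150 × √(1/12 + 1/24)) − 1.96) = Φ(2.828 − 1.960) = Φ(0.868) = 80.7% (78.5% with the t distribution).

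The HIV-RNA figure (0.7 log, SD 0.7) has the same ratio and the same power. The stated 36 is reproduced and is not in question.

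**2. Time needed per patient.**

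- Three cycles: 3 × 8 = 24 weeks (Overview). Control visits also end at week 24 (Table 4).
- Closing visits: up to 14 days = 2 weeks (Table 5).
- Total: 24 + 2 = 26 weeks from first dose or study entry.

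**3. Latest start that still finishes by week 52.**

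| Case | Weeks needed | Latest start |
| --- | --- | --- |
| Bare 24 weeks, no closing visits | 24 | 52 − 24 = week 28 |
| On schedule with closing visits | 26 | 52 − 26 = week 26 |
| Control week-24 visit at its +3-week limit | 29 | 52 − 29 = week 23 |
| Two cycles each delayed by 2 weeks | 30 | 52 − 30 = week 22 |

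For IL-2 patients, pre-therapy visit 1 may come up to 45 days (6.4 weeks) before first dose. The on-schedule limit then corresponds to a visit 1 by 26 − 6.4 = week 19.6. Sections VII.D.3, VIII.A and IX.A give different limits on cycle delay (11, two and eight weeks). They need reconciling, and longer delays bring the latest start forward.

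**4. Patients unfinished at one year.** The accrual lengths are assumptions. With even accrual of 36 over A weeks and 26 weeks needed, the finished share is min(1, 26/A).

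| A (weeks) | Per month | Finished | Unfinished |
| --- | --- | --- | --- |
| 26 | 6.0 | 36 | 0 |
| 30 | 5.2 | 31 | 5 |
| 39 | 4.0 | 24 | 12 |
| 52 | 3.0 | 18 | 18 |

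**5. Effect on the endpoint (illustrations).**

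- *HIV-RNA.* Assume the trapezoidal rule with IL-2 samples at weeks 0, 1 (day 8), 4 (day 29) and 8. The day-8 value then carries (4 − 0)/2 = 2 weeks of weight: 2/24 = 8% of a 24-week mean but 2/8 = 25% of an 8-week mean. The Introduction reports transient two- to three-fold rises at day 5 with twice-daily subcutaneous dosing, which is 0.30 to 0.48 log. A rise of that size at day 8 would add 0.025 to 0.04 log to a 24-week mean and 0.075 to 0.12 log to an 8-week mean. Controls have no matching sample.
- *CD4+.* The Introduction's randomized trial of continuous-infusion IL-2 reports about +37 against −5 cells per month, a gap of 42. If this were linear, the time-weighted difference over T months is 42 × T/2. At 24 weeks (5.54 months) that is 116 cells. With even 52-week accrual, mean follow-up capped at 24 weeks is 24 × 28/52 + 12 × 24/52 = 18.5 weeks (4.26 months), giving about 89 cells, or 23% less. That regimen included antiretrovirals, so only the direction carries over.
- *No post-baseline value.* With 52-week accrual, about 8/52 × 36 = 5.5 patients would have under 8 weeks of follow-up. About a third would be controls, possibly with no value after baseline.

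**The case against.** The strongest reply is that the clause need not bite. It can be read as the later of the two dates, and the Overview's demand for 36 completers favours that reading. The protocol foresees several sites, and at about 6 patients a month nobody is cut short. Both points stand: the harm depends on a reading and on an accrual rate that the text does not settle. They do not remove the ambiguity.

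The 24-week period is also an inference from the cycle length and Table 4. That is correct, and the missing horizon is part of the problem.

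A reader might go further in four ways that the documents do not support.

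- *Long accrual is already planned.* The flow cytometry appendix says "For a total of 840 tests during a period of two years". This is a reagent-supply estimate, follows a list of optional antibodies and does not mention enrolment.
- *The one-year analysis is an unplanned interim look.* The cut-off is specified in advance as the final analysis. The protocol says only: "There will be no interim analyses of efficacy data for the purposes of early study termination". No second efficacy test is described, so neither a contradiction nor an inflated error rate follows.
- *Power drops to that of the finished patients alone.* That would be about 64% with 24 and 52% with 18. The plan analyses by intention to treat, and partial follow-up can enter a time-weighted mean, so these figures describe an analysis that the protocol does not propose.
- *Safety data are lost.* Section XI.A follows safety through the post-treatment evaluation and requires serious events to be reported for 6 months after IL-2. Nothing says that collection stops at one year.

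**Conclusion.** The concern holds as an ambiguity with a real possible consequence. Read as the earlier date, the trigger permits a final analysis before the 36 patients have completed three cycles. That happens if the last patient starts after about week 26, or about week 23 if the control visit window is used in full. On assumed even accrual over 39 or 52 weeks, 12 or 18 of 36 would be unfinished; over 26 weeks, none.

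If it happened, both primary comparisons would shift towards early values, unequally by arm because early sampling differs. The HIV-RNA shift illustrated above is small beside the 0.7 log difference the trial is sized for. It still matters to the stated aim of showing virological neutrality.

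The documents do not show that truncation will occur. The sample size calculation itself is sound. This should be fixed, but it does not invalidate the design.

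**What to change.** Delete the one-year alternative and state: *The final analysis will be conducted after the last randomized patient has completed Post-Study Visit 2 or, for a patient who has withdrawn, after the date on which that visit was due.* Adding 'whichever is later' to the existing sentence would also keep the analysis from running before patients have finished.

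If a calendar stop is needed for practical reasons, the protocol should say which condition governs, define study initiation, fix the period for the time-weighted mean, and say how incomplete follow-up enters it.

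The change costs one sentence and a later readout if accrual is slow. With accrual over A weeks the analysis falls at about week A + 26. That is 39 + 26 − 52 = 13 weeks past the one-year mark for 39-week accrual and 26 weeks past it for 52-week accrual.

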### B. SUBCUTANEOUS (SC) IL-2

Despite the ability to administer CIV IL-2 safely to HIV-infected individuals, it is likely that such a regimen will be inappropriate for widespread clinical use. A less intrusive regimen of IL-2 would afford greater scope for clinical utility. The administration of IL-2 by subcutaneous injection has been evaluated in a number of clinical trials. One study, originally enrolling 18 patients and since amended to recruit a further 48 subjects with CD4+ cell counts >500 cells/mm3 is ongoing. The maximal tolerated dose of SC IL-2 was 15 MIU/day administered for five days every 8 weeks. Toxicities were similar, although generally less severe, to those observed with administration of CIV IL-2. Most patients also experienced local reactions characterized by erythema, tenderness and occasional nodularity. In common with observations derived from studies of CIV IL-2 in HIV disease an analysis of data from the original 18 patients has revealed the following trends: patient tolerance is directly related to HIV disease stage, higher baseline CD4+ counts are predictive of greater CD4+ increases in response to therapy and a favorable CD4+ response is generally disclosed within the first three treatment cycles (Figure 6).

Figure 6.

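### The analysis section does not name the pooled IL-2 v control contrast on which the 80% power rests, and its ANOVA makes no stated use of the two baseline samples

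*Protocol*

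**What the plan says.** The primary endpoints are the time-weighted mean changes from baseline in CD4+ count and in plasma HIV-RNA (section VIII.E.1).

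On power, section VIII.E.2 states that "a total of 36 patients randomized in the ratio of 2 SC IL-2:1 control participant will give 80% power of detecting an increase" of 150 cells/mm3 in the IL-2 group, with an SD of 150 cells/mm3. For HIV-RNA it takes a "standard deviation of 0.7 log copies/ml" and a difference of 0.7 log. Both are effects of 1 SD at a two-sided 5% level.

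On the test, section VIII.E.3 says: "Formal analysis will compare the randomized treatments in terms of time-weighted changes from baseline using ANOVA methods", or non-parametric equivalents. It names neither a contrast nor a covariate.

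On the number of groups, the document gives two descriptions:
- Section V.A: "There will be 3 treatment arms (1 control; 2 IL-2". Table 2 lists 12, 12 and 12.
- Section I (Synopsis): two regimens, no therapy (12) and IL-2 at either dose (24).

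On baseline, section VIII.B schedules flow cytometry and a plasma sample for HIV load at both pre-therapy Visit 1 and Visit 2 for all patients. Section II.B reports, as a trend in the first 18 patients of one subcutaneous IL-2 study, that "higher baseline CD4+ counts are predictive of greater CD4+ increases in response to therapy".

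**The concern.** The power statement and the test statement should describe the same comparison. Here the first is a two-group contrast. The second is tied to a term, the randomised treatments, that the document defines in two ways. In a three-arm trial an ANOVA of the randomised treatments can mean an overall F-test with 2 numerator degrees of freedom, two dose-by-dose comparisons, or a single pooled contrast. These do not have the same power, and only the last has the stated 80%. The trial is open label and has two primary endpoints, so the choice among them is better fixed before data are seen.

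The second part concerns efficiency. Baseline CD4+ and HIV-RNA are measured twice in everyone before treatment, and the stated method does not say that they enter the model. With 12 controls, any precision available at no cost is worth having.

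**Working it through.** **Inputs from section VIII.E.2 and Table 2.** Two-sided alpha 0.05; effect / SD = 150/150 = 0.7/0.7 = 1.0; 24 IL-2 patients (12 + 12) and 12 controls. Because the standardised effect is 1.0 for both endpoints, each result below applies to both.

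**1. The plan's own figure.** Noncentrality = 1 / sqrt(1/24 + 1/12) = 1 / sqrt(0.125) = 2.83.
- Normal approximation: Φ(2.83 − 1.96) = 80.7%.
- Noncentral t, 34 df: 78.5%.

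The stated 80% is therefore right for the pooled contrast. The dropout figures fit the same contrast: with 20% loss (19.2 v 9.6) the difference detectable at 80% power is 166 (normal) to 172 (t) cells/mm3 against the stated 175, and 0.78 to 0.80 log against the stated 0.8.

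**2. Pooled contrast within a three-arm ANOVA.** Same noncentrality, 36 − 3 = 33 df: 78.4%. Keeping three arms in the model costs essentially nothing if the pooled contrast is the one tested.

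**3. Omnibus F-test of three arms, both doses at +1 SD.** In SD units the arm means are 0, 1, 1 and the grand mean is 2/3. Lambda = 12 × [(2/3)² + (1/3)² + (1/3)²] = 12 × 6/9 = 8.0. Noncentral F with 2 and 33 df: 67.5%. About 48 patients (3 × 16) would be needed to pass 80% (81.4%).

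**4. How far that depends on equal dose effects.** Holding the average effect of the two doses at 1 SD:

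| Dose effects (SD) | Lambda | F-test power |
|---|---|---|
| 1.0 / 1.0 | 8.00 | 67.5% |
| 0.9 / 1.1 | 8.24 | 68.9% |
| 0.75 / 1.25 | 9.50 | 75.4% |
| 0.5 / 1.5 | 14.00 | 90.3% |

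**5. One dose v control (12 v 12), 1 SD.** Noncentrality = 1 / sqrt(1/12 + 1/12) = 2.45; noncentral t, 22 df: 64.9%. The protocol claims no power for this comparison, so the figure contradicts nothing. It does show that the 80% cannot be carried over to a single dose.

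**6. Baseline adjustment, pooled contrast.** If r is the correlation between baseline and change within arm, the residual SD is multiplied by sqrt(1 − r²) and the noncentrality becomes 2.83 / sqrt(1 − r²). Three arms plus one covariate leave 36 − 4 = 32 df. The documents give no r, so it is assumed:

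| Assumed r | Noncentrality | Power |
|---|---|---|
| 0 | 2.83 | 78.3% |
| 0.3 | 2.96 | 82.0% |
| 0.4 | 3.09 | 84.9% |
| 0.5 | 3.27 | 88.6% |

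If r is zero the adjustment loses about 0.1 percentage point against step 2 (78.4% to 78.3%).

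**The case against.** A reader might infer that the trial's 80% power simply becomes 67%. The documents do not support that. Nothing in section VIII.E.3 fixes an omnibus three-group test, and much of the text points to pooling. The Synopsis describes two regimens. The Objectives set IL-2 against no therapy and ask no dose-comparison question. The sample-size section speaks of a single IL-2 group. The sentence just before the quoted one in VIII.E.3 counts every IL-2 dose level in the treated patients' data. A planned pooled contrast is itself an ANOVA method. All of this stands, so the 67% is conditional on an omnibus test. It is also conditional on equal dose effects. The single effect size in VIII.E.2 is compatible with that, and so is the near-equal CD4+ rise at two subcutaneous doses (34% and 38%) reported in section II.B, but it remains an assumption.

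A reader might also take the missing covariate as an error. It is not. No covariate is named and none is ruled out, and covariates are commonly left to a statistical analysis plan, which is not at hand. The trend in section II.B comes from 18 treated patients and concerns CD4+ only. It may reflect effect modification as much as prognosis, and it says nothing about HIV-RNA.

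Nor does a chance baseline imbalance carry over in full to the treatment estimate, because the endpoint is already a change from baseline. Assume a baseline SD of 150. The arm difference in baseline then has a standard error of 150 × sqrt(0.125) = 53 cells. With r of 0.3 to 0.5 in size and equal SDs, an imbalance of that size shifts the estimate by about 16 to 27 cells, and this variation is already within the SD of change used for power.

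What remains is that the analysis section does not name the contrast that was powered, that the document's two counts of the randomised groups leave room for another, and that data already collected have no stated use in the model.

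**Conclusion.** The point holds as an improvement to the analysis wording. The 80% is correct for the pooled 24 v 12 contrast (78.5% by t, 80.7% by normal approximation) and for that contrast only. The formal test is stated without naming it. Under pooling nothing is lost. Under an omnibus F-test with both doses at 1 SD, power is 67.5%, about 11 points below the pooled t figure, and the gap closes or reverses as the doses differ more.

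The gain from baseline adjustment is real if baseline and change are correlated. Its size, about 82% to 89% at r of 0.3 to 0.5, rests entirely on that assumed range.

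**What to change.** In section VIII.E.3, replace the sentence on the formal analysis with wording such as:

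> *Time-weighted change is analysed by ANCOVA with randomised arm (three levels) and the corresponding baseline value (mean of pre-therapy Visits 1 and 2, same definition in all arms). The primary test is the 1-df contrast of the two IL-2 arms combined against control. Dose-specific differences are secondary, with 95% confidence intervals.*

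In section VIII.E.2, add that the 80% applies to this pooled contrast only. Bring the Synopsis and section V.A into line on the number of randomised groups.

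The common baseline definition matters because IL-2 patients have a further pre-cycle sample before dosing and controls have a week 0 sample; Visits 1 and 2 are shared by everyone.

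The cost is a change of wording. It needs no extra patients, visits or samples.

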### F. Long term management

Following completion of this protocol all patients should continue in follow-up. An additional protocol will be undertaken to provide continuing treatment to patients on the basis of their original randomization.

